**Methods/Design:**

This is an economic study with a transversal design. The contingent valuation method will be used to estimate the user's willingness to pay (WTP) for the care received from the primary care nurse and the willingness to accept [compensation] (WTA), were this service eliminated. A survey that meets the requisites of the contingent valuation method will be constructed and pilot-tested. Subsequently, 600 interviews will be performed with subjects chosen by systematic randomized sampling from among those who visit nursing at twenty health centers with different socioeconomic characteristics in the Community of Madrid. The characteristics of the subject and of the care received that can explain the variations in WTP, WTA and in the WTP/WTA ratio expressed will be studied. A theoretical validation of contingent valuation will be performed constructing two explanatory multivariate mixed models in which the dependent variable will be WTP, and the WTP/WTA relationship, respectively.

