The cutoff points will be decided by consensus of the research team following the pilot test. The questions in the pilot test on WTP and WTA will be made in an open format. In the questionnaire, the payment cards will include the value 0, and subsequently there will be a question that differentiates so-called "protest zeros" (do not accept the question itself), from the inability to make the payment.

The third and final section of the survey will collect, at least, the following characteristics, which will be transformed into independent variables in the study:

- Characteristics of the center: Rural/urban; Average income of the area

- Sociodemographic characteristics:

- Age in years.

- Sex: male/female

- Employment situation: active worker/unemployed or student/pensioner not retired/retired

- Education level attained: no education/primary/secondary/university

- Social class: (Categories I, from highly specialized professions to V, least specialized).

- Income level: sum of total weighted family income (Total/N^0.5^)

- Characteristics of use of service:

- Frequency: Number of nursing visits in last year

- Type of visit (depending on place of care): health center/domicile

- Type of visit (depending on type of service): promotion and prevention activities; care/monitoring pathologies/chronic processes; identification/monitoring of care plans; diagnostics and therapeutics procedures.

- Need of use of the service:

- Number of chronic pathologies suffered (requiring care for more than six months)

- Hospital admissions in last year (yes/no)

- Health-Related Quality of Life (HRQL) measured by EuroQol 5D

- Type of living arrangements: alone/with partner only/family nucleus/extended family nucleus. Family APGAR

- Caregiver of another person due to illness or incapacity. Yes/no

- Satisfaction with service: AMABLE questionnaire

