### Analysis of the data

The value provided by WTP and WTA will be selected for the descriptive analysis and these will be treated as continuous variables, which will be defined by their measures of central tendency and dispersion.

Continuous independent variables will be defined by the same parameters, and discrete variables by an estimate of the proportions and their confidence intervals of 95%. For an estimate of the confidence intervals the variance inflation factor caused by the type of sampling in conglomerates will be taken into account. Consistency of WTP and WTA will be evaluated in a subgroup of subjects by the intraclass correlation coefficient (ICC). To calculate the consistency of the response, the WTP and WTA question will be repeated by telephone to 100 randomly selected subjects, which enables estimating an ICC of around 0.9 with a minimum precision of 7.5%, with a confidence of 95% [18]. Evaluation of the consistency of the response, though this will depend considerably on interpersonal variability, will serve to evaluate the internal validity of the result [19]. The relationship between WTP and WTA will be measured by Pearson's correlation coefficient or Spearman's rho, as well as the ICC.

Univariate analysis will be performed to study the association of the independent variables with WTP, employing parametric tests for continuous variables that are distributed according to a normal distribution and non-parametric tests for the rest.

To validate the model and study the WTP/WTA relationship, two multilevel mixed linear models will be constructed. The variables referring to the individual will constitute the first level, and contextual variables (referring to the clusters or health centers) will make up the second level [20]. The model will be explanatory, given the design of the study. In case the contextual variables do not explain a significant part of the variance we will resort to classical multilevel models with robust estimators of the regression coefficients (Eicker-White estimator) that minimize the problems of heteroscedasticity [21]. The dependent variable of the models will be WTP or the WTP/WTA ratio, net or softened in its logarithmic expression. The independent variables will be introduced depending on their explanatory role in the model, and the final model will be chosen by the principles of maximum parsimony.

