## Discussion

Identifying the attribution of economic value to a health service that does not have a direct price at the time of use is relevant because it can be a way of incorporating patient preferences to health policy decision-making. It has been pointed out that one of the challenges of economic evaluation is the evolution from an expression of mere rationalism in the form of establishing normative behaviours to constituting a way of making preferences explicit [22], and it is in this framework that this project is designed.

Successfully identifying the value attributed to the service can only be complete validating the results in the construct of welfare theory [18], relating the values obtained to health needs, satisfaction with the service received and socioeconomic situation.

Defining a profile of "loss aversion" referring to the service evaluated is also relevant. Characterizing subjects who show less willingness to do without the service provides planners with another element of judgment of people's preferences. This approach has been used in our setting for the evaluation of the visit to the family physician with results that speak of the strength of the method [23].

As to potential limitations of the study we note questions of how representative the sample is, any information biases and those that pertain to the method itself.

With respect to how representative it is, because this is a sampling of users the probability of including those who most use the service increases and this can add more weight to use value in detriment of non-use values (altruistic and of opportunity or option).

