Possible information biases could limit the results of the study to some extent. The collection of variables such as frequency or number of pathologies will be provided by the family nurse with the patient's consent, but expressing social and economic self-positioning may be problematic. To minimize this resistance, we will also use the card format, allowing the person interviewed to only have to answer the letter of the category in which that person's answer if included. The quality of the design of the questionnaire will also be determining. Because the description of the scenario can have implications for the WTP expressed [24], we have chosen as realistic a description as possible, referring to a good obtained at the previous moment. If we can make a perfect description of the product, the market and the context of the transaction this will improve the validity and reliability of the result. This is why the design of the survey is viewed as one more phase of the research project.

Collecting WTP and WTA in a payment card format can produce biases, by varying in a specific range (yeah-saying bias). To limit this, the question is posed in two phases, each with a different payment card. The idealness and the advantages and disadvantages of the payment card compared with other formats and other methods to estimate WTP have been widely discussed; however, it is a commonly accepted tool [25]. Strategic bias and hypothetical bias, inherent to the contingent valuation method, cannot be avoided in this study. The first refers to the subject's tendency to express an unreal WTP, influenced by that person's intuition with respect to the study's objective (for example, refers to a low WTP if the person believes that this will influence the final price, if the service were ever paid for). We can value this tendency, but not avoid it, by studying how the WTP/WTA ratio behaves. The hypothetical bias reflects the difference in a subject's behavior when faced with hypothetical payments and in the real market. This bias is very difficult to establish, although it is more frequent in *ex-ante *studies than when the product being valued is known, which is our case. To evaluate the validity of the measure we will utilize the only approach feasible in this case. We will examine the congruence of the characteristics of the subject who expresses a certain WTP in the framework of economic welfare theory, and the reliability of the measure in a subgroup of patients.

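### Theoretical validity rests on the effects of socioeconomic situation, need and satisfaction on WTP, but the final model is chosen by maximum parsimony with no protection for those variables

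*Protocol article*

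**What the plan says.** The Abstract (Methods/Design) gives the models their purpose: "A theoretical validation of contingent valuation will be performed constructing two explanatory multivariate mixed models". The Discussion says what validation consists of. Identification of value is complete only when the results are validated within welfare theory, by "relating the values obtained to health needs, satisfaction with the service received and socioeconomic situation". On validity of the measure it adds: "We will examine the congruence of the characteristics of the subject who expresses a certain WTP in the framework of economic welfare theory", alongside a reliability check in a subgroup.

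Under Analysis of the data, the models are multilevel linear models of WTP and of the WTP/WTA ratio. The text says "The model will be explanatory, given the design of the study". Selection is then fixed in one sentence with two parts. The first part governs entry: "The independent variables will be introduced depending on their explanatory role in the model". The second part governs what is finally kept, and there the plan commits itself as follows: "the final model will be chosen by the principles of maximum parsimony". A preceding univariate step relates each independent variable to WTP.

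No section says that income, need or satisfaction stay in the final model, or that a fuller model is reported beside it.

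**The concern.** A validity test of this kind concerns named effects. Its result is the adjusted estimate and interval for each, whether large, null or of the wrong sign. A parsimony rule asks a different question, namely which variables can be left out. Applied to the same data with no exemption, it can remove the quantities that the test needs.

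Two things are at stake:
- A weak theory variable may have no adjusted estimate in the final model. For income this matters because it overlaps with social class, education, employment and area income, all listed under Measuring tools and variables included. Its unadjusted association is therefore a poor substitute.
- If the rule keeps variables on the strength of their estimates, weak effects that survive are on average too large, and the usual intervals take no account of the selection.

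**Working it through.** **The plan's own figures.** The article sizes the study for a mean, not for regression slopes. Reading 0.15 SD as a half-width, (1.96/0.15)² = 170.7, against 170 stated. The design effect is 1 + 29 × 0.075 = 3.175, and 171 × 3.175 = 542.9, against 543 stated. These figures reproduce but say nothing about the size of effects on WTP. No expected slope, selection threshold or covariate correlation is given, so everything below is assumed except the 600 subjects, the 20 centres of 30 and the ICC of 0.048 from the previous paper.

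**Hand check of the mechanism.** Take 20 uncorrelated standardised candidates analysed within centre.
- Residual variance is 1 − 0.048 = 0.952, and residual degrees of freedom are 600 − 20 − 20 = 560. The standard error of a slope is √(0.952/560) = 0.0412.
- With a two-sided 5% cut, a slope survives only if its estimate exceeds 1.96 × 0.0412 = 0.081.
- The chance of survival is 1 − Φ(a), with a = (0.0808 − β)/0.0412. The mean estimate given survival is β + 0.0412 × φ(a)/(1 − Φ(a)).
- β = 0.05: a = 0.75, survival 23%, mean 0.05 + 0.0412 × 0.302/0.227 = 0.105, or 2.1 times the truth.
- β = 0.10: a = −0.47, survival 68%, mean 0.10 + 0.0412 × 0.358/0.679 = 0.122, or 1.2 times the truth.

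**Simulation.** The set-up was 600 runs per setting, 20 candidates of which 3 are true theory variables with equal slopes, predictor correlation 0 or 0.3, and backward elimination at p < 0.05 or by a BIC-type cut (|t| > √ln 600 = 2.53). Ranges run over the two rules and two correlations.

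| True slope (SD per SD) | Each theory variable kept | All three kept | Mean surviving estimate ÷ truth | Coverage of nominal 95% CI when kept |
|---|---|---|---|---|
| 0.05 | 10–25% | 0–1% | 2.1–2.7 | 51–86% |
| 0.08 | 28–49% | 1–12% | 1.4–1.8 | 77–94% |
| 0.10 | 47–68% | 3–31% | 1.22–1.52 | 84–96% |
| 0.15 | 81–96% | 48–87% | 1.02–1.15 | 94–98% |
| 0.20 | 98–100% | 93–100% | 1.00–1.01 | 95–96% |

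The hand check agrees with the uncorrelated 5% case (survival 22% and 68%, ratios 2.09 and 1.22).

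A second set of assumptions (15 covariates correlated 0.2, ICC 0.075, 5% cut, 1,500 runs) gives the same picture. At a slope of 0.08, income is dropped in 46% of runs and averages 0.121 when kept (0.121/0.08 = 1.51). At 0.05 it is dropped in 73% and averages 0.110 when kept (2.2 times). At 0.15 the surviving mean is 0.161 (1.07 times).

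**With the theory variables retained.** In the full model the mean estimate is 0.98 to 1.02 times the true slope in every setting of the first simulation. Holding only the three theory variables in, and applying elimination to the other 17, gives the same range.

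**The case against.** The best reply is that the damaging rule is assumed. The article mentions no stepwise procedure and no threshold. It enters variables by explanatory role, which may mean theory-led entry, with parsimony trimming only redundant socioeconomic proxies. The exact criterion is a detail that an article may leave to a fuller document. This stands as far as it goes: a reader might infer that variables are kept because they are significant, but the text does not say so. It does not remove the point, because the article itself states the parsimony rule and makes no exception for the variables that form the test.

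A reader might also infer that validation becomes circular, or that evidence against theory vanishes. The documents do not support either. Losing a true effect makes congruence harder to show, not easier. No false-confirmation rate under a null effect has been calculated. Congruence may be judged mainly on presence and direction, which inflation need not change. A variable's absence from the final model is itself visible, and the univariate step still shows its unadjusted association with WTP. The subgroup reliability check is untouched by selection. What is lost is the adjusted estimate and its interval.

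Finally, the simulations work within centre, while the plan draws centres from the upper and lower income terciles. A mixed model may therefore hold more information on income than they allow, and income might be dropped less often.

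**Conclusion.** The point holds in a limited form. The article rests theoretical validity on the relation of WTP to socioeconomic situation, need and satisfaction in its multivariate models, and then subjects those same variables to a parsimony rule. That mismatch is in the text and depends on no simulation.

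The consequences depend on a data-driven criterion and on effect size. Overstatement is material for slopes up to about 0.10 SD per SD, small at 0.15 and negligible at 0.20. It is an average direction for weak effects, not a fixed amount. Slopes, number of covariates, correlations and cut-offs are all assumptions. Nothing was calculated for the WTP/WTA ratio model, and the congruence criterion is stated for WTP, so no size can be claimed for the loss-aversion profile. This is worth correcting before analysis, but it does not invalidate the design.

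**What to change.** Add one or two sentences under Analysis of the data:
- Pre-specify, with expected signs, the variables that carry the validity test: equivalised family income as the socioeconomic measure, number of chronic pathologies and EuroQol 5D for need, and the AMABLE score for satisfaction. If the team considers another socioeconomic or need item essential to the theory, it should be named now.
- Keep these in the final WTP model whatever their p-value, and report their estimates and 95% confidence intervals as the validity result.
- Apply parsimony only to the remaining covariates, and state the criterion.
- Use the same retention rule in the WTP/WTA ratio model for consistency.

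Forcing in the centre variables (rural/urban, area income) is optional. If it is done, it must be reconciled with the stated fallback for when contextual variables do not explain a significant part of the variance.

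The cost is four degrees of freedom if each variable enters as one term, or six with the two centre variables, out of 600 subjects. Intervals for other covariates become slightly wider. No new data or interviews are needed.

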### Ethical and legal aspects

All the research process will be governed by the ethical principles contained in the Declaration of Helsinki (revision Seoul 2008). Those persons who are included will be asked for their consent in writing to participate in the study and will be advised that all the data will be stored and treated anonymously, complying with the requisites established in national legislation. The study has the favorable report of the Ethics Review Board of the Hospital Fundación Alcorcón.

## Discussion

Identifying the attribution of economic value to a health service that does not have a direct price at the time of use is relevant because it can be a way of incorporating patient preferences to health policy decision-making. It has been pointed out that one of the challenges of economic evaluation is the evolution from an expression of mere rationalism in the form of establishing normative behaviours to constituting a way of making preferences explicit [22], and it is in this framework that this project is designed.

Successfully identifying the value attributed to the service can only be complete validating the results in the construct of welfare theory [18], relating the values obtained to health needs, satisfaction with the service received and socioeconomic situation.

Defining a profile of "loss aversion" referring to the service evaluated is also relevant. Characterizing subjects who show less willingness to do without the service provides planners with another element of judgment of people's preferences. This approach has been used in our setting for the evaluation of the visit to the family physician with results that speak of the strength of the method [23].

As to potential limitations of the study we note questions of how representative the sample is, any information biases and those that pertain to the method itself.

With respect to how representative it is, because this is a sampling of users the probability of including those who most use the service increases and this can add more weight to use value in detriment of non-use values (altruistic and of opportunity or option).

Possible information biases could limit the results of the study to some extent. The collection of variables such as frequency or number of pathologies will be provided by the family nurse with the patient's consent, but expressing social and economic self-positioning may be problematic. To minimize this resistance, we will also use the card format, allowing the person interviewed to only have to answer the letter of the category in which that person's answer if included. The quality of the design of the questionnaire will also be determining. Because the description of the scenario can have implications for the WTP expressed [24], we have chosen as realistic a description as possible, referring to a good obtained at the previous moment. If we can make a perfect description of the product, the market and the context of the transaction this will improve the validity and reliability of the result. This is why the design of the survey is viewed as one more phase of the research project.

Collecting WTP and WTA in a payment card format can produce biases, by varying in a specific range (yeah-saying bias). To limit this, the question is posed in two phases, each with a different payment card. The idealness and the advantages and disadvantages of the payment card compared with other formats and other methods to estimate WTP have been widely discussed; however, it is a commonly accepted tool [25]. Strategic bias and hypothetical bias, inherent to the contingent valuation method, cannot be avoided in this study. The first refers to the subject's tendency to express an unreal WTP, influenced by that person's intuition with respect to the study's objective (for example, refers to a low WTP if the person believes that this will influence the final price, if the service were ever paid for). We can value this tendency, but not avoid it, by studying how the WTP/WTA ratio behaves. The hypothetical bias reflects the difference in a subject's behavior when faced with hypothetical payments and in the real market. This bias is very difficult to establish, although it is more frequent in *ex-ante *studies than when the product being valued is known, which is our case. To evaluate the validity of the measure we will utilize the only approach feasible in this case. We will examine the congruence of the characteristics of the subject who expresses a certain WTP in the framework of economic welfare theory, and the reliability of the measure in a subgroup of patients.

Therefore, successfully identifying in this project the attribution of economic value to a health service, such as a visit to nursing in primary care, and the definition of a "loss aversion" profile referring to the service evaluated, can constitute, despite the shortcomings of this kind of design, elements of interest for planning health services in our setting, enabling decision-making that incorporates the preferences expressed by the system's users.
